## Abstract

**Background:**

Workplace violence is an increasingly significant topic, particularly for staff working in mental health settings. The Centre for Addiction and Mental Health (CAMH), Canada’s largest mental health hospital, considers workplace safety a high priority and consequently has mandated staff safety training. For clinical staff, key components of this training are self-protection and team-control skills, which are a last resort when an individual is at an imminent risk of harm to self or others and other interventions are ineffective (eg, verbal de-escalation). For the past 20 years, CAMH’s training-as-usual (TAU) has been based on a 3D approach (description, demonstration, and doing), but without any competency-based assessment. Recent staff reports indicate that the acquisition and retention of these skills may be problematic and that staff are not always confident in their ability to effectively address workplace violence. The current literature lacks studies that evaluate how staff are trained to acquire these physical skills and consequently provides no recommendations or best practice guidelines. To address these gaps described by the staff and in the literature, we have used an evidence-based approach from the field of applied behavior analysis known as behavioral skills training (BST), which requires trainees to actively execute targeted skills through instruction, modeling, practice, and feedback loop. As part of this method, competency checklists of skills are used with direct observation to determine successful mastery.

**Objective:**

Our objectives are to evaluate the effectiveness of BST versus TAU in terms of staff confidence; their competence in self-protection and team-control physical skills; their level of mastery (predefined as 80% competence) in these skills; and their confidence, competency, and mastery at 1 month posttraining.

**Methods:**

We are using a pragmatic randomized controlled trial design. New staff registering for their mandatory safety training are randomly assigned to sessions which are, in turn, randomly assigned to either the BST or TAU conditions. Attendees are informed and consented into the study at the beginning of training. Differences between those consenting and those not consenting in terms of role and department are tracked to flag potential biases.

**Results:**

This study was internally funded and commenced in January 2021 after receiving ethics approval. As of May 2022, data collection is complete; half of the baseline, posttraining, and 1-month videotapes have been rated, and three-fourths of the interrater reliability checks have been completed. The analysis is expected to begin in late summer 2022 with results submitted for publication by fall 2022.

**Conclusions:**

The findings from this study are expected to contribute to both the medical education literature as well as to the field of applied behavioral analysis where randomized controlled trial designs are rare. More practically, the results are also expected to inform the continuing development of our institutional staff safety training program.

**International Registered Report Identifier (IRRID):**

DERR1-10.2196/39672

## Introduction

The promotion of health and safety in the workplace is globally recognized as a critical issue. Addressing workplace violence directly contributes to the achievement of several of the sustainable development goals set out by the International Labour Organization including health, gender equality, and decent work and economic growth [1,2]. According to the Centers for Disease Control and Prevention, workplace violence can be categorized into 4 types: criminal intent (the perpetrator has no legitimate relationship to its employees), customer or client (violence to employees from clients, family members, and visitors), worker-on-worker (horizontal violence), and personal relationship (perpetrator has a relationship to an employee outside of work setting) [3]. Globally, health care workers are at a higher risk of experiencing “customer or client” workplace violence than any other category of workers [4,5]. Two meta-analyses, representing 393,344 health care workers, demonstrated a 19.3% pooled prevalence of workplace violence in the past 12 months and 24.4% and 42.5% of respondents reported experiencing physical violence and psychological violence, respectively [6,7].

In Canada, 61% to 68% of nurses and personal support workers experienced a serious incidence of workplace violence, and 20% experienced at least 9 physical assaults in the last year [8]. In Ontario, health care workers, representing 11.7% of the province’s workforce, were also noted to be at the greatest risk of experiencing and being disproportionately affected by workplace violence compared to all other workers [9]. Within health care, psychiatric care facilities and their staff are at high risk for customer or client violence in the form of aggression from patients [10,11].

Experiencing workplace violence has been associated with negative psychological, physical, emotional, financial, and social consequences, which impact the staff’s ability to provide care and function at work [12]. More specifically, behavioral emergencies or psychiatric behaviors such as yelling, demanding, cursing, manipulating, acting out, or threatening danger are disruptive to the functioning of the unit and place the safety of everyone at risk [13].

In response, health care organizations have committed to creating a safe work environment by adopting a myriad of strategies [9]. In 2017, the Centre for Addiction and Mental Health (CAMH) adopted a major initiative to ensure the physical and psychological safety of all patients and staff. A priority component of this initiative is a mandatory training program for all new direct care staff that teaches trauma-informed crisis prevention, de-escalation skills, and, in particular, safe physical intervention skills. The physical skills curriculum focuses on self-protection and team control skills with the first set of skills targeting how staff can protect themselves when faced with physical violence and the second set related to physical restraint in the hospital. Manual restraint carries a risk of injury for all those involved and in some circumstances can provoke aggressive behavior and staff injuries [14].

The current curriculum (hereafter, “training-as-usual” [TAU]) was developed over 20 years ago. It uses the 3D approach (“describing,” “demonstrating,” and “doing” the skill through practice). However, this approach is not competency based and thus inconsistent with the contemporary directions in health care and education of using competency [15,16] and evidence-based approaches [17,18]. Furthermore, recent staff reports indicate that the skills acquired using this method are not always retained over time and that staff are not always confident about their ability to use them.

The study described in this protocol seeks to address some of these issues by evaluating 2 forms of training for all new clinical staff in a mental health care setting. We have used an evidence-based approach from the field of applied behavior analysis known as behavioral skills training (BST). BST is a competency and performance-based training model that requires trainees to accurately demonstrate targeted skills through a loop involving instruction, modeling, practice, and feedback. Checklists are used throughout the training to evaluate whether competency in a skill is achieved [19,20], and a predetermined threshold can be applied to these competency ratings to determine whether the skill has been mastered [20]. An important feature of BST is that skill rehearsal and trainer feedback are continued until the predetermined mastery criterion is achieved.

There is a large body of evidence that indicates that individuals who receive BST demonstrate significant improvement in targeted skills posttraining and maintain those skills over time and across settings [21-23]. This model has been used to train a wide range of participants including behavior analysts, parents, and educators to build safety-related skills and manage aggressive behavior [21,24].

The objective of this study is to compare the real-world effectiveness of BST and TAU in terms of physical safety skills acquisition and retention after 1 month as well as staff confidence in their use of these skills.

The following are the null hypotheses being tested: there will be no significant differences between BST and TAU in terms of (1) the competence scores or the percentage of study participants who attain mastery (predefined as a score of 80% or higher) for self-protection or team control physical skills at the end of the mandated training session; (2) the competence scores or the percentage of study participants that continue to demonstrate mastery at 1 month posttraining for either self-protection or team-control skills (retention); and (3) the percentage of study participants who express confidence in their skills at 1 month posttraining.

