The checklists (see self-protection checklist example, Multimedia Appendix 1) will be used during training for the BST sessions and for the baseline, posttraining, and 1-month study assessments for all study participants. On the training day, attendees will be asked individually to go to a separate room. They will be asked once to demonstrate each of the 11 skills prior to the start of training for baseline and just after the training for posttraining. Only those attendees who have consented to be study participants will have their baseline and posttraining assessments videotaped. For the 1-month follow-up, study participants will be asked to come in to have their skills assessed and videotaped. Videotaping will be done through WebEx (Cisco) and will be rated by a research team member using the predefined competency checklists. On these checklists, each skill component will be judged to be performed “correctly” or “incorrectly.” The final competency rating for each skill will be the percent of its component skills that were rated as correctly performed.

The reliability and validity of these ratings will be assessed using IOA calculations [28]. Prior to the study, raters had been trained on a test set of videotapes drawn from a previous study and had reached agreement levels of at least 90% for self-protection and team-control skills. For this study, all videotapes are rated by a primary rater. At the same time, a 30% random sample of videotapes from training months 1, 3, 4, 6, and 9 will be independently rated by a designated secondary (reliability) rater. IOA with the ratings from the primary rater will be calculated after every 2 videotapes rated by the secondary rater and, if the IOA is less than 90%, a recalibration discussion is held and recorded between the 2 raters with a third neutral rater available if needed to resolve any remaining differences. Recalibration decisions are then applied to all subsequent videotape ratings.

A predetermined threshold of 80%, consistent with clinical practice [29,30], is then applied to each competency rating to define skill mastery. Retention between posttraining and the 1-month follow up is measured in terms of whether the competency ratings changed as well as whether the percentage of study participants meeting the mastery threshold has changed.

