### Data Management and Statistical Analyses

Data from the competency checklists, completed by raters on the research team, and data from the self-reported evaluation completed by participants are collected via REDCap, which is CAMH’s designated web-based application for research data capture and then exported to Excel (Microsoft Corp) spreadsheets [31]. After data cleaning, these spreadsheets will be imported to a statistical software package (eg, SPSS, R) for analysis.

Testing of the 3 hypotheses will be done using repeated measures ANOVA. In addition, the study participants will be compared to all attendees in terms of their role and department to evaluate whether there are any striking differences despite our randomization methods. We also plan to assess the association between the frequency of physical skills used in the past month and our measures of skill competence, mastery, retention, confidence, and satisfaction.

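### Repeated measures ANOVA is named for all three hypotheses, but mastery, and confidence as worded, are yes/no outcomes that need a binary method

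*Protocol article*

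**What the plan says.** The null hypotheses at the end of the Introduction pair a continuous outcome with a binary one. Hypothesis 1 concerns "the competence scores or the percentage of study participants who attain mastery (predefined as a score of 80% or higher") at the end of training. Hypothesis 2 concerns competence scores or "the percentage of study participants that continue to demonstrate mastery at 1 month posttraining". Both refer to self-protection or team-control skills. Hypothesis 3 concerns only "the percentage of study participants who express confidence in their skills at 1 month posttraining".

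Variables Assessed explains where mastery comes from. Each skill gets a competency rating, the percentage of its components performed correctly, and a threshold of 80% "is then applied to each competency rating to define skill mastery". Retention is judged by change in the ratings and by "whether the percentage of study participants meeting the mastery threshold has changed". Confidence is collected on a 0-10 scale at baseline, after training and at 1 month.

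Data Management and Statistical Analyses then states: "Testing of the 3 hypotheses will be done using repeated measures ANOVA". It names no other method for the outcomes expressed as percentages.

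**The concern.** Once the 80% cut-off is applied, mastery is a 0/1 variable. Repeated measures ANOVA assumes errors that are roughly normal, equal variance across arms, and sphericity across time points. The variance of a 0/1 variable is p(1-p), so it is fixed by the rate itself. The trial is designed to look for rates that differ between arms and over time, and wherever they do, these assumptions fail.

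Hypothesis 3 has the same problem as worded. A percentage expressing confidence is binary, although the 0-10 score behind it is not.

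This is a stated mismatch and not a missing detail, because the protocol has already assigned one method to all three hypotheses. At stake are the standard errors and intervals for the arm differences in mastery, chiefly at 1 month, where the retention claim will be made.

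**Working it through.** **Inputs from the document.** 40 participants per arm (Sample and Sample Size); three assessments (Variables Assessed); mastery as an 80% cut-off; repeated measures ANOVA for all hypotheses. The article gives no mastery rate at any time point, so every rate below is an assumption. There is no stated figure on this point to reproduce.

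**Step 1: variance depends on the rate.** With variance p(1-p): 5% or 95% gives 0.0475; 90% gives 0.09; 60% gives 0.24; 50% gives 0.25. A common variance is impossible when rates differ this much.

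**Step 2: does the overall test break down?** 0/1 data were simulated for two arms of 40 and three time points, with identical rates in both arms, a latent within-person correlation of 0.2 or 0.5, and 4,000 runs per scenario. Session clustering was not modelled. Type I error of the group-by-time test at a nominal 5%:

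| Assumed rates (baseline / post / 1 month) | Uncorrected | Greenhouse-Geisser |
|---|---|---|
| 5 / 90 / 80% | 4.8%, 5.4% | 4.2%, 4.8% |
| 2 / 95 / 90% | 4.5%, 4.9% | 3.8%, 4.4% |
| 5 / 95 / 60% | 6.2%, 6.4% | 4.8%, 5.0% |
| 5 / 60 / 50% | 5.3%, 5.3% | 4.8%, 5.2% |
| 30 / 60 / 50% | 4.6%, 4.1% | 4.5%, 4.0% |

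(First figure: correlation 0.2; second: 0.5.) The test stays close to its nominal level.

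**Step 3: what happens to the arm difference at 1 month?** Suppose the contrast uses one error variance pooled over the six arm-by-time cells. With V the mean of the six cell variances:

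- pooled SE = √(2V/40)
- actual SE at 1 month = √((p₁(1-p₁) + p₂(1-p₂))/40)
- approximate coverage = 2Φ(1.96 × pooled SE / actual SE) - 1

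Example, BST/TAU rates of 5/5% at baseline, 90/50% posttraining and 70/40% at 1 month:

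- V = (0.0475 + 0.0475 + 0.09 + 0.25 + 0.21 + 0.24)/6 = 0.885/6 = 0.1475
- pooled SE = √(0.295/40) = 0.086
- actual SE = √(0.45/40) = 0.106
- ratio 0.81, coverage about 89%

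The same formulas over a range of assumed rates:

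| Baseline | Posttraining | 1 month | SE ratio | 1-month coverage |
|---|---|---|---|---|
| 2/2% | 95/60% | 60/40% | 0.75 | 86% |
| 5/5% | 90/50% | 70/40% | 0.81 | 89% |
| 10/10% | 90/70% | 70/50% | 0.83 | 89% |
| 20/20% | 90/50% | 70/40% | 0.91 | 92% |
| 20/20% | 80/60% | 60/40% | 0.91 | 93% |
| 30/30% | 90/50% | 70/40% | 0.95 | 94% |
| 30/30% | 95/70% | 90/70% | 1.04 | 96% |

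The interval is usually too narrow at 1 month. The last row shows that it can also be slightly too wide.

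**Step 4: the same contrast without pooling.** With variances specific to the time point, simulated coverage for 70% against 40% at 40 per arm was 94.0%. The loss in step 3 therefore comes from pooling.

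**The case against.** The strongest defence has three parts.

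First, repeated measures ANOVA is a conventional choice for the continuous competence scores, which hypotheses 1 and 2 also contain. That stands, and the linear model should stay for them.

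Second, the method is serviceable in practice. A reader might infer that ANOVA on mastery is outright invalid. Step 2 does not support that: the worst simulated type I error was 6.4%, and 5.2% with the Greenhouse-Geisser correction. The supportable term is mis-specified.

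Third, the interval problem depends on choices the article does not make. It does not say that contrasts will use a pooled error, and follow-up comparisons by time point would largely avoid the problem. This also stands, so the coverage figures are conditional.

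A reader might also infer that mastery runs from near 0% before training to near 100% after it. The document does not say so. It says only that participants are "asked once to demonstrate each of the 11 skills prior to the start of training for baseline". It gives no baseline rate and also asks at baseline about skill use in the past month. Training to criterion makes a ceiling plausible in the BST arm, but TAU has no mastery criterion (Table 1).

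Finally, how skill-level mastery is combined into one status per participant and domain is a detail that a fuller plan may hold. It is not counted as an error here.

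**Conclusion.** The point holds as a mismatch between outcome and method. The only test named for mastery, and for confidence as hypothesis 3 words it, assumes a variance structure that a 0/1 outcome cannot have when rates differ.

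The consequence is moderate and conditional. The overall group-by-time test is little affected. The 1-month interval may be mis-sized, with coverage of about 86% to 96%, if a pooled error term is used. Those figures rest on assumed rates, 40 per arm and no allowance for session clustering. The mismatch should be corrected, but it does not invalidate the trial or the analysis of the competence scores.

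**What to change.** Replace the single sentence on ANOVA with a method for each type of outcome.

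- **Competence scores, and confidence if analysed as a 0-10 score:** keep the linear repeated measures model. Reword hypothesis 3 to match if the score is what will be tested.
- **Mastery per participant in each domain, and any dichotomised confidence outcome:** use a binary method, such as logistic GEE with a small-sample correction or a logistic mixed model. Name a penalised or exact alternative for cells close to 0% or 100%, where ordinary logistic fits can fail. Keep the participant as the unit, since modelling each skill separately would change the target from the percentage of participants.
- **Session:** account for it, because Design, Setting, and Recruitment assigns sessions to BST or TAU.
- **Reporting:** give arm differences in percentage with 95% intervals at posttraining and at 1 month for mastery, and at 1 month for confidence.

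The cost is a little more analysis work and possibly slightly wider intervals. No new data are needed, and the article reports that analysis had not begun as of May 2022.

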Study participants complete self-reported evaluation forms covering descriptive information, confidence, training satisfaction, and frequency of skill use. The participants also provide information regarding their professional role and service department at CAMH. For confidentiality reasons, personal characteristics such as age and gender or sex were not provided to the research team, and, for the same reasons, we chose not to collect this information. All participants are asked to evaluate their confidence on a 0-10–point scale (0=not at all confident to 10=extremely confident) in using the 11 self-protection and team-control skills at baseline, immediately after the training, and at 1-month follow-up (Multimedia Appendix 2). All participants were asked to rate for satisfaction with the training on a 4-point scale immediately after the training and 1 month later. The number of times in the past month that self-protection or team-control skills were used is asked at baseline and 1-month posttraining. Finally, an open-ended item is provided in the posttraining assessment form for any comments that trainees want to communicate to the facilitators.

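### Hypothesis 3 is a percentage confident at 1 month, but confidence is a 0-10 rating taken at three times and the named test is repeated measures ANOVA

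*Protocol article*

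**What the plan says.** The third null hypothesis in the Introduction concerns "the percentage of study participants who express confidence in their skills at 1 month posttraining". It is a proportion, at one time.

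Variables Assessed describes the measurement differently. Participants give a number on a scale running "0=not at all confident to 10=extremely confident", and they do so "in using the 11 self-protection and team-control skills at baseline, immediately after the training, and at 1-month follow-up".

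Data Management and Statistical Analyses names one method: "Testing of the 3 hypotheses will be done using repeated measures ANOVA".

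The objectives are wider than the hypothesis. The abstract sets out to "evaluate the effectiveness of BST versus TAU in terms of staff confidence" and then lists, as a further item, "their confidence, competency, and mastery at 1 month posttraining". The Introduction's objective names skills acquisition and 1-month retention "as well as staff confidence in their use of these skills", and it gives no time for confidence.

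**The concern.** The hypothesis, the measurement and the test describe three different things: a proportion at one time, a rating at three times, and a comparison of means over repeated times. They cannot all be followed together.

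Hypotheses 1 and 2 do not have this gap for skills. Each names a competence score beside the mastery percentage, the percentage has an 80% threshold, and the two hypotheses cover the end of training and 1 month. Hypothesis 3 names only a percentage, with no threshold and one time.

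Two things are at stake. First, the reported test may not answer the stated hypothesis. Second, if the percentage is taken literally, a trial of 40 per group gives up precision, and the size of the difference depends on where the line is drawn. The Discussion asks whether either method is better at improving or at maintaining confidence. Improving needs the baseline rating and maintaining needs the posttraining one, and hypothesis 3 as worded uses neither.

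**Working it through.** **1. The plan's own figure.** Sample and Sample Size gives 40 per group for 80% power at a medium to large effect, without a number. I assume two-sided alpha 0.05 and independent participants. The detectable standardised difference is d = (1.960 + 0.842) × √(2/40) = 0.626 by the normal approximation, or 0.634 by the t test. That lies between the conventional 0.5 and 0.8, so the stated size is consistent with its wording for a comparison of means. I use d = 0.635 below.

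**2. The two readings of hypothesis 3.**

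- *ANOVA on the 0-10 ratings.* This fits the measurement and the named method, and nothing is lost by splitting. But it compares mean ratings over time, so it does not test a percentage at 1 month.
- *Percentage at 1 month.* This fits the hypothesis. But there is no repeated measure and no mean rating to compare. It also needs a cut-off and a rule for turning 11 ratings into one status per person, and the article gives neither.

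**3. Information kept if the rating is split.** For a normal variable and a small effect, relative efficiency is φ(z_p)² / [p(1 − p)], where p is the proportion classed as confident.

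- p = 0.5: 0.3989² / 0.25 = 0.637, and 80 × 0.637 ≈ 51.
- p = 0.8: 0.2800² / 0.16 = 0.49, and 80 × 0.49 ≈ 39.

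**4. Power at d = 0.635, 40 per group.** For the mean rating, 0.635/√(2/40) = 2.840, and 2.840 − 1.960 = 0.880, giving 81% (80% by the t test). For the split rating, p₁ = Φ(Φ⁻¹(p₀) + 0.635), and power = Φ{[(p₁ − p₀) − 1.96√(2p̄(1 − p̄)/40)] / √([p₀(1 − p₀) + p₁(1 − p₁)]/40)}.

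| TAU confident | BST confident | Power | n per group for 80% |
|---|---|---|---|
| 10% | 25.9% | 46% | 91 |
| 30% | 54.4% | 60% | 64 |
| 50% | 73.7% | 59% | 65 |
| 80% | 93.0% | 40% | 108 |
| 90% | 97.2% | 26% | 178 |

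**5. Dependence on the cut-off.** Assume a TAU mean of 6.5, SD 2 and d = 0.635 (BST mean 6.5 + 0.635 × 2 = 7.77), with ratings rounded to whole points from 0 to 10.

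| Cut-off | TAU | BST | Difference (points) | Power |
|---|---|---|---|---|
| ≥4 | 93.3% | 98.4% | 5 | 20% |
| ≥6 | 69.1% | 87.2% | 18 | 50% |
| ≥8 | 30.9% | 55.4% | 24.5 | 60% |
| ≥10 | 6.7% | 19.4% | 12.7 | 39% |

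The mean of the same rounded rating gives about 79%.

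**6. Gain from the baseline rating.** With baseline correlation r, residual variance falls by the fraction r². For r = 0.3, 0.5 and 0.7 that is 9%, 25% and 49%. Power at d = 0.635 becomes about 85%, 91% and 98% (normal approximation, against 81% unadjusted). The article gives no value of r.

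**The case against.** The strongest reply is that this is a condensed article. A cut-off, and a rule for combining 11 ratings, could sit in an analysis plan or in Multimedia Appendix 2, which is not shown. That stands. The missing cut-off alone is not a finding, and a reader should not infer that one will be picked with the data in hand: the documents do not show that.

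The information loss is also conditional. A reader might infer that the trial will certainly discard a third to a half of its information. If the ANOVA is run on the raw ratings, it discards none.

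A reader might also infer that posttraining confidence has no test. The documents do not support that either. Repeated measures ANOVA needs more than one time, and run on the ratings it could use the baseline and posttraining values. That confidence just after training is an objective at all is an inference from the abstract listing confidence twice, supported by the Introduction's untimed objective and by the collection schedule.

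Finally, a percentage confident is easy to interpret and parallels the mastery percentage. That is a fair reason to report it, but not to make it the only form of the hypothesis.

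None of this removes the mismatch. Even with a cut-off fixed elsewhere, a yes/no outcome at one time does not fit the named test.

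**Conclusion.** The point holds as an internal mismatch in one of the three hypotheses. The wording of hypothesis 3, the way confidence is measured and the named test cannot all stand, and the hypothesis is narrower in time than the abstract's objectives and the data collected.

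The size depends on which reading is followed. On the ANOVA reading there is no loss of power, but the stated hypothesis is not the one tested. On the percentage reading, about 64% or 49% of the information is kept at the two splits shown. At an effect the trial could detect with about 80% power on the mean, no split tried exceeds about 60%.

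These figures are illustrations. They assume a normal underlying rating, two-sided alpha 0.05, d = 0.635 and, in the cut-off table, a TAU mean of 6.5 and SD of 2; none of these is in the article. They ignore clustering by training session and loss at 1 month, so the absolute powers are optimistic. Confidence is high in the mismatch and only moderate in how much it would matter.

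**What to change.** Restate hypothesis 3 as no BST-TAU difference in mean 0-10 confidence at 1 month, and also at posttraining. Summarise confidence by a stated rule over the 6 self-protection skills and over the 5 team-control skills. Analyse it in a model for the continuous rating, adjusted for the baseline rating. Amend the analysis section to match. If a percentage confident is kept, make it secondary or descriptive, fix its cut-off in advance, and use a binary-outcome method if it is tested.

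No new data are needed, since all three ratings were collected. The cost is an endpoint change after data collection: Results reports that raw collection was complete and cleaning had begun by May 2022, with analysis still to come. The change therefore needs a dated amendment recording that it was made without sight of results by arm.
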